## Abstract

**Background:**

Both short sleep duration and circadian rhythm misalignment are risk factors for metabolic dysfunction, but the underlying mechanisms are unknown. The goal of this study is to examine how sleep duration and circadian alignment predict changes in cardiometabolic risk factors over a 12-month period, and test cognitive function and hedonic eating tendencies as potential mechanisms.

**Methods:**

We will recruit a sample of 120 working aged adults with BMI 25–35 kg/m^2^ (overweight to class I obesity). The protocol includes 5 visits over a 12-month period. Study visits include wrist actigraphy to measure sleep behaviors, 24-h diet recalls, dim light melatonin collection, a computerized neurobehavioral assessment, eating in the absence of hunger task, and frequently sampled IV glucose tolerance test.

**Discussion:**

The results of the TIME study will advance the understanding of how both short sleep duration and circadian misalignment contribute to behavioral aspects of obesity and metabolic dysfunction.

**Trial registration:**

ClinicalTrials.Gov, NCT04759755, registered retrospectively February 13, 2021.

## Background

More than 1/3^rd^ of adults are overweight or obese [1] which contributes to major causes of preventable death including cardiometabolic diseases (cardiovascular disease, type 2 diabetes) as well as some cancers. There is increasing evidence that both short sleep duration and circadian rhythm misalignment adversely impact cardiometabolic health [2]. A meta-analysis demonstrated short sleep duration was associated with a 37% higher risk for diabetes mellitus, 16% higher risk for cardiovascular disease and 38% higher risk for obesity [3]. In addition, circadian misalignment, defined as mistimed sleep in relation to internal circadian rhythm, is also an independent predictor of cardiometabolic health [4, 5]. When exposures to short sleep duration and circadian misalignment are combined in laboratory experiments, research has demonstrated these exposures have an additive effect [6, 7]. However, little is known about how chronic exposure to sleep loss and circadian misalignment in daily life affect cardiometabolic health.

Our laboratory has focused on the translation of laboratory research to real-world settings and studying the effects of common types of circadian misalignment in daily life. In our previous study, we examined the role of circadian timing and alignment (sleep timing in relation to the circadian phase marker of dim light melatonin onset) on obesity and cardiometabolic risk factors in a sample of healthy young to middle aged adults with habitual sleep duration of at least 6.5 h [8]. We discovered that circadian misalignment, rather than timing per se, was associated with greater caloric and carbohydrate intake, consuming a greater number of meals, and in overweight participants, insulin resistance [8, 9].

A limitation of our study design was that by excluding individuals with short sleep duration, we could not examine the role of sleep duration in this study. Given that more than half of potential participants were ineligible for our study due to short sleep duration (particularly those with later sleep times), this demonstrates how the interaction between sleep duration and circadian alignment may be particularly important to understanding risk in daily life. In addition, results of our study also suggest that neurobehavioral determinants of increased hedonic eating (e.g., impulsivity) may play a role in the cardiometabolic consequences of short sleep duration and circadian misalignment.

This paper describes the protocol of our current study: the circadian Timing, Information processing and Metabolism (TIME) study. The first aim of the study is to examine the interaction between sleep duration and circadian misalignment in predicting dietary behavior, neurobehavioral aspects of hedonic eating behaviors, dietary intake and cardiometabolic risk factors. The study also will examine neurobehavioral measures in the morning versus the evening and finally evaluate how sleep and circadian misalignment predict 12-month change in cardiometabolic risk factors. Recruitment for this study began in 2019, therefore we also describe the protocol adaptions we made due to the COVID-19 pandemic.

## Methods/Design

### Participants and eligibility criteria

Participants will include adults aged 18–55 years with BMI ranging from 25.0–34.9 kg/m^2^who have habitual sleep onset times between 10:30 pm and 3:00 am, verified by 7 days of wrist actigraphy. Exclusionary criteria include: 1) High risk or presence of sleep disorders as assessed by the questionnaires and overnight OSA screening; 2) Diabetes diagnosis or HbA1c (glycated hemoglobin) > 7.0%; 3) History of cognitive or neurological disorders; 4) Presence of major psychiatric disorders, current alcohol or substance abuse as determined by screening questionnaires; 5) Unstable or serious medical illness; 6) Overnight shift work or travel over 2 or more time zones in the past 2 months; 7) Use of hypnotic, stimulant or medications known to affect melatonin concentrations such as beta blockers, daily NSAIDs or antidepressants; 8) Current smoking, 9) Daily caffeine intake > 300 mg, 10) Pregnant or lactating.

### Procedure

#### Recruitment and prescreening

Participants will be recruited from the community using flyers, mailing letters, research registries (researchmatch.org) and online postings (Reddit, Craig’s list, Facebook). Interested participants will complete screening questionnaires online via the REDCap system and then study staff will follow-up with phone calls to review key criteria, administer the substance abuse and eating disorders questionnaires and discuss information about the study. If interested and eligible, participants will be scheduled for an in-person study visit and tentatively scheduled for the follow-up visits.

#### Study visits

The study consists of 5 in-person visits (Fig. 1).

**Fig. 1 Fig1:**
[figure not shown]
Procedure. * Indicates visits conducted in randomized counterbalanced order. Neuro= neurobehavioral testing, circ= circadian testing, met= metabolic testing

#### Visit 1

Screening/baseline. Participants who are potentially eligible based on the online or telephone prescreening will complete an in-lab screening (visit 1) which involves informed consent, blood draw for HbA1c, height and weight measurement to determine BMI criteria, one night with an Apnea Link monitor (Resmed Inc.) to screen for presence of OSA and 7 days of wrist actigraphy (brand, model) to screen for sleep timing criteria. After reviewing the screening data, research staff will call participants to inform them of their eligibility. Participants who are excluded due to high risk for OSA or diabetes will be provided with a results letter and recommended to discuss with a physician.

#### Visits 2 and 3

These visits will be scheduled in counterbalanced order (Day A and B), with approximately 14 days between sessions, to reduce carryover effects in the neurobehavioral testing. Day A starts at 9 am and consists of neurobehavioral testing in the morning session, questionnaires and free time mid-day (quiet laboratory activities such as watching TV or reading) and circadian phase assessment, (dim light melatonin onset, DLMO), in the evening. Participants will be discharged at their habitual bedtime. For Day B, participants arrive at the University of Utah Center for Clinical and Translational Science outpatient location at 8:30 am. Participants will be instructed to fast for the 8 h prior to their visit. Participants will undergo a frequently sampled IV glucose tolerance test from 9:00 am to approximately 12:30 pm. After this test, participants will go to the behavioral sleep medicine laboratory and will be provided with lunch. The afternoon will consist of completing self-report questionnaires and then participants will have free time for quiet activities in the laboratory. Snacks will be provided ad libitum. The neurobehavioral testing will start at 7:45 pm and discharge will occur around 9:30 pm.

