## Discussion

This study extends results of laboratory-based experimental research to evaluate the impact of these sleep/circadian factors on adults in their daily lives. Results will advance understanding of the mechanisms by which sleep and circadian rhythms link to the neurobehavioral processes that affect eating behaviors, including impulsivity and the underlying metabolic risk factors. We will be able to examine how time of day affects the ability to delay gratification and hedonic eating behaviors and also whether sleep and circadian alignment affect change in cardiometabolic risk over 1-year period.

Strengths of this study include detailed, objective measurement of sleep and circadian timing, gold-standard methods of metabolic testing, and use of standardized neurobehavioral tests and ecologically valid tests of hedonic eating behaviors. On the other hand, limitations to this study include a highly screened sample free from depression, sleep disorders and substance abuse (which limits generalizability). The ongoing effects of the COVID-19 pandemic on enrollment and retention on research studies may affect the power to observe our hypothesized relationships, despite our best efforts to overcome these challenges.

In conclusion, this protocol will examine key neurobehavioral and metabolic processes that are hypothesized to link sleep loss and circadian rhythm misalignment to increased risk for cardiometabolic disorders. Results will advance the translation of laboratory research by increasing the understanding of how circadian rhythm misalignment and short sleep duration interact to increase risk for cardiometabolic diseases in naturalistic settings.

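### In Aim 2, every evening test falls on the metabolic-test day and every morning test on the circadian day, so the paired contrast does not isolate time of day

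*Protocol article*

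**What the plan says.** The protocol article, Visits 2 and 3, describes two day types with fixed content.

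- **Day A:** "Day A starts at 9 am and consists of neurobehavioral testing in the morning session". Melatonin sampling follows in the evening. No fast and no glucose test are stated for this day.
- **Day B:** "Participants will be instructed to fast for the 8 h prior to their visit". Then "Participants will undergo a frequently sampled IV glucose tolerance test from 9:00 am to approximately 12:30 pm". Then "After this test, participants will go to the behavioral sleep medicine laboratory and will be provided with lunch". The day ends as follows: "Snacks will be provided ad libitum. The neurobehavioral testing will start at 7:45 pm and discharge will occur around 9:30 pm".

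Only the sequence of the two days varies: "These visits will be scheduled in counterbalanced order (Day A and B), with approximately 14 days between sessions, to reduce carryover effects in the neurobehavioral" tasks.

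Data analysis, Aim 2, makes calories consumed the primary outcome. It compares morning with evening by paired t-test, then regresses the difference on DLMO time, adjusted for sex, age and race/ethnicity. The secondary outcomes (delay discounting, stop signal, processing speed, sleepiness, hunger, appetite) follow the same scheme.

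The Discussion gives the intended reading: "We will be able to examine how time of day affects the ability to delay gratification and hedonic eating behaviors".

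**The concern.** A paired morning-evening difference reads as a time-of-day effect only if the two sessions otherwise differ by nothing that acts on the outcome. Here they also differ in the fast, several hours of IV glucose testing with 22 sampling times, a provided lunch and access to unrestricted snacks. Each could plausibly affect later food intake, and some could affect fatigue or task performance. Such effects could create, hide or reverse a difference between morning and evening.

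The planned analysis has no term for Day B procedures or for food eaten that day. The limitations in the Discussion do not mention the problem. A separate analysis plan could not cure it, because the aliasing comes from the visit schedule.

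**Working it through.** **The plan's own figure.** The article gives no power figure for Aim 2. The only one given is for Aim 1 (Sample size justification), and it reproduces: (1.960 + 0.842) × 32.1 / (57 × √96) = 2.802 × 32.1 / 558.5 = 0.161 per minute, as stated. With a covariate correlation of 0.4, 0.161 / √(1 − 0.16) = 0.176, also as stated. Nothing in this point depends on those figures.

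**Is time of day separable from day content?** The two possible sequences give four cells:

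| Sequence | Visit | Day content | Test time |
|---|---|---|---|
| A then B | 2 | A | morning |
| A then B | 3 | B | evening |
| B then A | 2 | B | evening |
| B then A | 3 | A | morning |

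The correlation of test time with day content is 1.0. The correlation of test time with visit order is 0.0. A design matrix with intercept, test time and visit order has rank 3. Adding day content leaves the rank at 3.

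**What the paired difference estimates.** Let τ be the evening-minus-morning effect, δ the effect of Day B content and π the effect of the second visit.

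- A then B: expected difference = τ + δ + π
- B then A: expected difference = τ + δ − π
- Average over the two sequences: τ + δ

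Counterbalancing removes π, as intended. It leaves δ whole.

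**How much could it matter?** The documents do not give δ, so the shifts below are assumptions. They are in SD units of the paired difference, with the 96 complete participants, a two-sided 5% test and τ = 0. The noncentrality is d√96 on 95 degrees of freedom.

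| Assumed Day B shift d | d√96 | Chance of a significant result |
|---|---|---|
| 0 | 0 | 5% |
| 0.1 | 0.98 | 16% |
| 0.2 | 1.96 | 49% |
| 0.3 | 2.94 | 83% |
| 0.5 | 4.90 | 99.8% |

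For scale, the shift detectable with 80% power is 2.802 / √96 = 0.286 SD.

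**What happens to the DLMO slope?** Write a participant's Day B effect as δ₀ + δ₁ × DLMO and the true slope as β. The regression of the difference on DLMO time then has δ₀ in its intercept and a slope of β + δ₁. A Day B effect that is the same for everyone does not touch the slope. One that varies with DLMO time, for example through snack intake, does.

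Day B was also not identical for all. Under Metabolic measures, insulin was part of the glucose test at first and was later dropped. That could make δ differ between early and later participants.

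**The case against.** Several points on the other side are sound.

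- **Pre-load.** Under Eating behaviors, the task begins with oatmeal, which partly evens out immediate hunger. It does not undo the glucose test or variable intake earlier in the day.
- **Task placement.** The text on Visits 2 and 3 does not name the eating task, and Figure 1 is not shown. Its place in these sessions is inferred from the morning-evening calorie outcome in Aim 2. For the neurobehavioral outcomes no inference is needed.
- **Snack timing.** A reader might infer that participants snack right up to the evening task. The text does not say so: about 7 hours 15 minutes separate the end of the glucose test from 7:45 pm, and a food-free interval may stand in the full protocol.
- **The fast.** Eight hours before an 8:30 am arrival is 12:30 am, so it is essentially overnight, and lunch follows it. What participants eat before Day A is not stated. The fast is the weaker part of the contrast.
- **Inherent differences.** Some extra earlier intake belongs to any evening test. The glucose test does not.
- **Planned measurements.** Hunger, appetite and sleepiness are already morning-evening outcomes and will help interpretation. The DLMO regression is also already planned.
- **Discussion wording.** It states what the study will be able to examine. It does not assert that an effect exists.

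A reader might also infer that the bias exceeds the detectable effect. The documents give no snack energy, no compensation rate and no SD for calories, so that cannot be shown. Aim 2 may also have more than 96 pairs, since it uses visits 2 and 3 while the 20% attrition is a study-wide allowance.

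None of this separates time of day from day content.

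**Conclusion.** The point holds as a limit on interpretation. In the paired Aim 2 contrasts, time of day is completely aliased with Day A/B content, whatever the sample size. They estimate the evening of the metabolic-test day against the morning of the circadian day. For the calorie outcome this rests on the inferred placement of the eating task; for the neurobehavioral tests it follows directly from the text.

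The direction and size of any bias are unknown, and the rejection rates above only illustrate assumed shifts. The documents do not support saying that the counterbalancing is faulty, since it balances visit order as intended. Nor do they support saying that Aim 2 as a whole fails: the DLMO slope is protected against a constant Day B effect, though not against one that varies with DLMO time. Aims 1 and 3 do not use the morning-evening contrast.

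**What to change.** 1. **Restate the contrast.** Describe the Aim 2 paired comparison, for all its outcomes, as the evening of the metabolic-test day versus the morning of the circadian day. Qualify the time-of-day statement in the Discussion and list the aliasing among the limitations.
2. **Shift the inferential weight.** Make the planned regression of the difference on DLMO time the main Aim 2 inference. Add an indicator for whether insulin was used in that participant's glucose test. State that the slope is still biased if Day B effects, such as snack intake, vary with DLMO time.
3. **Document Day B intake.** For remaining participants, weigh or standardise the snacks and record or fix their timing before the evening task, with a before/after indicator in the model. This reduces or measures one component only: the glucose test stays on Day B, and data already collected are not helped.
4. **Limit covariate adjustment.** Use same-day intake and pre-test hunger only in sensitivity analyses. They may be mediators of time of day, hunger is itself an Aim 2 outcome, and adjusting for them cannot remove the aliasing.

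The cost is a less ambitious conclusion, two indicator terms and a minor change to snack handling.

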#### Follow-up visits

Participants will complete wrist actigraphy, HbA1c, BMI and body fat assessments at 6 months (visit 4) and 12 months (visit 5). Visit 5 will also include a circadian phase assessment (DLMO).

Phone follow-ups: We will conduct follow-up surveys at 3 and 9 months to maintain engagement with the participants.

#### Procedure adaptations during COVID-19 Pandemic

In order to reduce risk for COVID exposure among participants and staff, we made the following adaptations in our procedure: We will minimize time in the room with the participant, for example instructing the participant to self-collect and store saliva samples with the use of a two-way video monitor, requiring KN95 or N95 facemasks by staff and participants at all times except when alone in a room with a closed door and finally, and offering the option for a limited contact at the 12-month follow-up visit: In order to reduce in-person exposure and preserve our primary outcome measures for visit 5 (HbA1c, body measurements collected in the lab, wrist actigraphy and questionnaires completed at home).

#### Compensation

Participants will be paid up to $850 for study participation if they complete all elements of the study. They will also receive additional compensation based on performance on the neurobehavioral tests (up to $30 per session).

### Measures

#### Screening measures

Participants will complete questionnaires to screen for insomnia symptoms using the Insomnia severity index [10], restless legs syndrome using the International Restless Legs Questionnaire [11], risk for obstructive sleep apnea using the STOP questionnaire [12], depression using the Patient Health Questionnaire-8 [12], substance alcohol use using the Alcohol Use Disorders Identification Test [13], drug use using the National Institutes on Drug Abuse (NIDA) Modified Assist questionnaire [14], and selected items to screen for symptoms of eating disorders (restriction, binging, purging) from the Eating Disorders Diagnostic Scale [15].

#### Wrist actigraphy protocol

Participants will wear the Actiwatch Spectrum (Philips/Respironics, Bend, OR) on the nondominant wrist for 7 days at screening/baseline, prior to the phase assessment, at 6 and 12 months. Actiwatches will be set with 30-s epoch length and medium sensitivity. Actigraphic sleep parameters will be calculated using Actiware-Sleep 6.1.1 software (or the current version) with default settings and included the following variables: sleep onset time, sleep offset time, and sleep duration. Actigraphy files will be scored using a standardized protocol using inputs of marker use, light and activity [16].

#### Circadian measures

Saliva samples will be collected every 30 min in the 7 h prior to habitual sleep onset time, as determined by actigraphy at screening. DLMO time will be calculated for each profile, and defined as clock time when salivary melatonin concentrations rise above the average of three low daytime values plus twice the standard deviation of the baseline values [17]. Circadian alignment will be calculated as duration between DLMO and average sleep onset time in adjacent week, consistent with our prior study [8].

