### Sample size justification

Sample size determinants: We aim to enroll 120 subjects and, accounting for a 20% attrition rate, this will allow us to collect complete data on 96 subjects. Based on standard deviations of 32.1 mg*L^2/(mmol*mU*min) or insulin sensitivity index [33] and 57 min for circadian alignment, we can estimate the minimum detectable effect at 80% power to be 0.161 mg*L^2/(mmol*mU*min) /min for a univariable linear regression. Further assuming a correlation of 0.4 between the covariates and circadian alignment, we can estimate the minimum detectable effect (of circadian alignment on insulin sensitivity index) in the multiple regression to be 0.176 mg*L^2/(mmol*mU*min). We will use all available resources to recruit the planned number of participants, but due to slowdowns and stoppages related to the COVID-19 pandemic, we may not reach the full sample size planned for this study. If we enroll 100 participants rather than 120, it will increase the minimal detectable effect size by 9.5%. If we enroll 110 participants, it will increase the minimal detectable effect size by 4.5%.

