### Missing data

Our longitudinal analyses employ restricted maximum likelihood estimation which will provide approximately unbiased results in the presence of missing data so long as the pattern of missingness follows a missing at random pattern after accounting for the non-missing measurements of the variables included in the model [34]. Nonetheless, fully sequential multiple imputation will be the primary method used to address missing data [35]. The imputation models will include all variables in the respective outcome models plus additional variables identified as likely related to the risk of missingness or the values of the variables being imputed. In particular, any nonmissing baseline, 6 week or 12 week or 1-year measurements for a given outcome will be included in imputation models for that outcome. The application of multiple imputation will assure that statistical inferences are approximately unbiased so long as the mechanism of missingness follows a missing at random [MAR] structure [36] after accounting for both the analysis variables and additional auxiliary variables in the imputation models.

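### A DLMO later than the last saliva sample cannot be recorded, and missing-at-random imputation would ignore the upper bound this puts on circadian alignment; the cost is precision, not material bias

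*Protocol article*

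**What the plan says.** Under Circadian measures, the article fixes the sampling window: "Saliva samples will be collected every 30 min in the 7 h prior to habitual sleep onset time, as determined by actigraphy at screening". The description of Visits 2 and 3 closes the evening: "Participants will be discharged at their habitual bedtime". DLMO needs an observed crossing; it is "defined as clock time when salivary melatonin concentrations rise above the average of three low daytime values plus twice the standard deviation" of those baseline values. The exposure follows from it: "Circadian alignment will be calculated as duration between DLMO and average sleep onset time in adjacent week".

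Baseline alignment is the main predictor in Aim 1 (insulin sensitivity index) and Aim 3 (HbA1c over 12 months). DLMO time itself is the predictor in the Aim 2 regression.

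On missing values the plan says: "Nonetheless, fully sequential multiple imputation will be the primary method used to address missing data". The imputation models are to contain every variable of the outcome model plus auxiliary variables, and the claim of approximately unbiased inference is made conditional on missingness at random.

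**The concern.** Three choices are fixed that do not fit together: a window that ends at sleep onset, an exposure that needs a crossing inside that window, and a missing-data method that assumes missingness does not depend on the missing value.

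If melatonin rises only after the last sample, there is no DLMO, and the reason is the size of alignment itself. That missingness is not at random. The value is not wholly unknown either: alignment must be below the interval from the last sample to sleep onset. An ordinary imputation model, fitted to participants whose DLMO was seen, does not use this and places these participants near the middle of the observed distribution.

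At stake are precision for the main predictor and the low-alignment end of its range. The article defines the phenomenon of interest as "circadian misalignment, defined as mistimed sleep in relation to internal circadian rhythm". Sleep that starts before melatonin onset fits that description, although the article does not say which direction of the interval counts as misaligned.

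**Working it through.** **1. The plan's own figure.** Inputs from Sample size justification: SD of the insulin sensitivity index 32.1, SD of alignment 57 min, N = 120 × 0.8 = 96, 80% power, covariate correlation 0.4; two-sided 0.05 from Data analysis.

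- Univariable: (1.960 + 0.842) × 32.1 / (57 × √96) = 0.161.
- Adjusted: 0.161 / √(1 − 0.4²) = 0.176.

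Both stated values reproduce, so 57 min is the spread on which the plan relies. The mean of alignment is not given.

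**2. What can be observed.** Let A = (average sleep onset in the adjacent week) − DLMO. A DLMO is recorded only if it falls no later than the last sample. An unobserved late DLMO therefore implies

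A < (adjacent-week average sleep onset) − (time of last sample).

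If the last sample is at screening sleep onset and sleep timing has not shifted, the bound is 0. It is above 0 if the last sample is earlier or sleep onset in the adjacent week is later, and below 0 if sleep onset has moved earlier.

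**3. Share affected.** Assumptions: A is normal with SD 57, and the mean is 90, 120 or 150 min. Share = Φ((bound − mean)/57).

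| Assumed mean | Bound 0 | Number of 96 | Bound 30 min (further assumption) |
|---|---|---|---|
| 90 | Φ(−1.58) = 5.7% | 5.5 | Φ(−1.05) = 14.6% |
| 120 | Φ(−2.11) = 1.8% | 1.7 | Φ(−1.58) = 5.7% |
| 150 | Φ(−2.63) = 0.4% | 0.4 | Φ(−2.11) = 1.8% |

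**4. Where imputation puts them (bound 0).** For means 90, 120 and 150, the true average alignment of the unobserved group is −24, −21 and −18 min. Normal imputation from the outcome gives averages of 87, 109 and 135 min. Across the scenarios of step 3, 93 to 99% of imputed values fall above the bound.

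**5. Effect on the slope (bound 0).** Simulation with n = 96, true slope 0.176 and no other covariates:

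| Assumed mean | SE, all DLMO seen | SE, missing-at-random imputation | SE, imputation within the bound |
|---|---|---|---|
| 90 | 0.056 | 0.067 | 0.057 |
| 120 | 0.057 | 0.061 | 0.057 |
| 150 | 0.056 | 0.057 | 0.056 |

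The increases are 0.067/0.056 = 1.20, 0.061/0.057 = 1.07 and 0.057/0.056 = 1.02. A repeat simulation gave about 20%, 9% and 1%. Imputing within the bound leaves at most about 2% (0.057/0.056).

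A complete-case analysis loses a similar amount: the adjusted minimum detectable slope moves from 0.176 to 0.203, 0.186 and 0.179.

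**6. Bias.** In a large simulated sample (bound 0), missing-at-random imputation changes the slope by +2.4%, +0.7% and +0.3% for means 90, 120 and 150. The complete-case slope is essentially unbiased, because selection is on the exposure.

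**The case against.** The strongest reply is that the Missing data section never names DLMO or alignment. It opens with the longitudinal analyses, and its one specific instruction concerns outcomes. How to score a profile that never crosses is detail that a full protocol or analysis plan may hold. This stands in part: that ordinary imputation would be applied is a reading of the phrase on outcome-model variables, not an explicit statement. The window, the exposure definition and the primary method are nevertheless all fixed in the article, and as written they conflict.

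The size also rests on assumptions. Mean alignment is not given, the normal shape is assumed, and the source of the 57 min is not explained; if it is an SD of observed values, it already reflects some truncation. Eligibility (sleep onset from 10:30 pm, no high risk of sleep disorder, no overnight shift work) could thin the tail further. The 30-minute bound is an added assumption, since the article does not say that the last half hour goes unsampled. All of this stands.

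Two stronger readings are tempting. One is that every profile without a crossing reveals a late DLMO. It does not: the threshold uses only three values plus twice their SD, so a noisy baseline or low secretion can also hide a rise. The other is that the main estimates will be biased. Step 6 does not support that under a linear relation.

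**Conclusion.** The point holds in a limited form. A DLMO after the last sample cannot be recorded, so alignment is then missing because of its own low value, and the stated method, read as covering alignment, ignores a known upper bound.

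The number affected cannot be derived from the article. With SD 57 min, a normal shape and an assumed mean of 90 to 150 min it is 0.4 to 5.7%; within that range of means, about 15% is reached only if the last 30 minutes are also taken as unobserved. The consequence is a standard error larger by roughly 1 to 20% at a bound of 0, together with loss of the low-alignment tail. For scale, the article itself reports a 9.5% rise in the detectable effect if 100 rather than 120 enrol.

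A reader might infer that the most misaligned participants will in fact be lost in numbers, or that the trial's conclusions would be wrong. The article supports neither: incidence may be near zero, and the slope is not materially biased if the relation is linear. Severity: minor to moderate.

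**What to change.** Add a field giving the reason for each missing DLMO, and one rule to the imputation section:

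- **Censored.** Where samples are valid and complete and melatonin stays at low baseline levels to the last sample, treat alignment as at most the adjacent-week average sleep onset minus the last-sample time. Impute from the same model, restricted to values within that bound.
- **Ordinary missing.** Failed assays, missed visits, and profiles that cannot be scored because of a high or noisy threshold or low secretion stay under the missing-at-random model.
- **Reporting.** Give the number censored and one sensitivity analysis, either with these values set at the bound or complete-case.

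The cost is one data field and one rule, with no extra samples or visits. The drawback is reliance on the tail of the imputation model for a few participants. Values placed there by the model also do not restore evidence on non-linearity in that tail, so the planned check for non-linear relationships should be read over the observed range only.
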